Participants who experience a treatment limiting toxicity (TLT), defined as a toxicity to ampho B treatment that results in discontinuation of that treatment prior to day 14 and prior to receipt of a total of 8.4 mg/kg ampho B, may either remain in Step 1 and receive an alternative treatment, such as liposomal ampho B, if available, or may enter Step 2 and receive study-provided fluconazole 800 mg or the maximum locally approved daily dose.

Participants who complete Step 1 will enter Step 3 after approximately 2 weeks.

For participants in Step 2, if negative CSF culture results are obtained prior to week 10 (i.e., negative culture results are available at or before week 8 from a sample collected at least 2 weeks previously), the participant will enter Step 3 and will receive fluconazole 400 mg daily (or 600 mg daily if receiving RIF) until week 10. It is possible that participants in Step 2 will not enter Step 3.

At week 10, all participants will enter Step 4 and receive fluconazole 200 mg daily through week 24.

Stage 2 (Dose Validation)

In Stage 1, when either the MTD of fluconazole is reached or the week 10 visit for the final participant randomized to the 2000 mg/day cohort is completed, all data through week 10 on all participants will be reviewed; the protocol will be amended before Stage 2 (Dose Validation) of the study opens. In Stage 2, participants will be randomized to receive an induction treatment of either an ampho B-based regimen or one of several doses of fluconazole **or fluconazole plus 5FC** at or below the MTD identified in Stage 1 (see A5225/HiFLAC Stage 2 Flow Chart).

Stage 1 and Stage 2 Evaluations

Participants will be monitored for safety and toxicity throughout the study period.

The primary efficacy outcome measure is the change in quantitative CSF culture for Cryptococcus at week 2. At screening or entry and again at week 2, CSF samples for culture will be collected from all participants. Additional CSF samples will be collected and cultured from participants on study treatment at weeks 4, 6, 8, and 10, as necessary until a negative culture is obtained. Treatment failure for any participant is defined as a positive culture from a CSF sample collected at week 10 and that is read by or at week 12.

Pharmacokinetic (PK) samples will be obtained at specified time points from all participants enrolled in fluconazole induction cohorts (see section 10.0 for sampling information).

DURATION 24 weeks

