The primary efficacy outcome measure is the change in quantitative CSF culture for cryptococcus. During screening or at entry, CSF samples for culture will be collected from all participants. At week 2, CSF samples will again be collected from all participants and will be cultured. Additional CSF samples will be collected and cultured at weeks 4, 6, 8, and 10, until a negative culture following 2 weeks of incubation is obtained. Treatment failure for any participant is defined as a week 10 CSF culture (which is read by or at week 12) that is positive for *C. neoformans*.

If a week 10 CSF culture is positive (by or at week 12), participants may discontinue study treatment and be treated according to local standard practice, at the discretion of the site investigator. Participants who discontinue study treatment prematurely should be encouraged to remain on study, off study treatment and should be encouraged to return for the week 24 visit.

PK samples will be obtained at specified time points from all participants enrolled in fluconazole induction cohorts (see section 10.0 for sampling information). Plasma, urine, serum, and CSF samples will be collected from all participants and stored for retrospective evaluation of novel diagnostic methodologies (collection schedule is presented in section 6.1).

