- - - 1. Management of Mycological Failure at Week 10

At week 10, participants with mycological failure (ie, whose most recent CSF culture is positive) may enroll in Step 4 or may, at the site investigator’s discretion, discontinue study treatment and instead be treated according to best standard local practice, administered by the site investigator. This may include, but is not limited to, switching to an alternative regimen with continued CSF monitoring every two weeks.

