The decision about which doses will be chosen for testing in Stage 2 will be based on: Stage 1 toxicity including the rates of DLT and also the grades and types of toxicity, dose modifications, the duration of treatment interruptions, and the rate of permanent treatment and study discontinuations, and general consideration of efficacy including early CM mortality, CNS clearance (both the rate of clearance and the proportion who clear), and early information on the duration of remission. An additional 24 participants will be randomized to each dose of fluconazole carried into Stage 2. The Stage 2 sample size for ampho B-based regimens will depend on how many fluconazole doses were tested in Stage 1 with the intent of having a total of 48 participants treated with ampho B between the two Stages. The randomization ratio will depend on how many fluconazole doses are tested and on the target ampho B sample size in this stage.

The target sample size of a total of 48 participants on a dose of fluconazole between Stages 1 and 2, and 48 on an ampho B-based regimen is based on:

- Ensuring that the width of a 90% confidence interval (CI) for culture negativity (early discontinuation or death = fail) within a dose or within ampho B-based regimens no wider than 25%.
- Detecting a difference in EFA of about 0.10 log10 CFU/ml CSF/day (about 67% of the s.d.) between two fluconazole doses or between a dose of fluconazole and ampho B with 90% power and a 2-sided 0.05-level test.
- Detecting a 25% difference (e.g. 50% vs. 75%) in efficacy between two fluconazole doses or between a dose of fluconazole and ampho B with 90% power (one-sided alpha=.10 test).
- Having the added ability to detect unusual or unexpected events that occur at a low rate, especially in consideration of those who might not be evaluable for toxicity given very early death. For example, if an unexpected and unacceptable event occurs at a rate of 5%, there is only a 64% chance of seeing one or more rare events in 20 participants evaluable for safety and an 87% chance of seeing one or more rare events in 40 participants evaluable for safety combined over both Stages.

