The precision with which the rate of IRIS can be estimated will depend on the proportion of participants who initiate ART and the time on study between ART initiation and when participants go off study. It should be remembered that this study is relatively short, and it is recommended that ART not be initiated until Step 3 or 4. The time from ART start to development of IRIS (i.e., any IRIS or specifically CNS IRIS) and the proportion with IRIS at pre-specified time points such as 8 or 12 weeks will be estimated by Kaplan Meier methods. The 95% CI on the proportion with IRIS at specified time points will be calculated using Greenwood’s formula.

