### 9.5 Analysis

9.5.1 Stage 1

Dose escalation is based on DLT and the decision rules as outlined above. As noted above, between-dose comparisons to select the fluconazole dose(s) to carry forward will largely be descriptive and not formally powered as all information will be factored into this decision.

9.5.2 Stage 2

In this pilot, we intend to combine the data over both Stages for the ampho B-based cohorts and for fluconazole doses that are tested in Stage 2. As noted above, only the confidence interval around the observed DLT rate in each dose will be adjusted for the dose escalation scheme. Analyses will employ appropriate methods such as Fisher’s exact test to compare dichotomous outcomes (e.g., Grades 3 and 4 events; CSF clearance before week 10) between doses or drugs, and t-tests or Wilcoxon tests to compare continuous covariates between two groups (or ANOVA or Kruskall-Wallis tests if three groups including ampho B). In the event all three fluconazole doses are evaluated in Stage 2, tests for trend such as ANCOVA, Cochran-Armitage and Jonckheere-Terpstra tests will be performed. Survival and other measures of time-to-event from study entry will be summarized with Kaplan-Meier estimates and, where appropriate, tested with log rank tests and possibly proportional hazards regression. The duration of the initial hospitalization will need to consider the duration of hospitalization preceding study entry. The focused neurological exam will be analyzed both on an item-by-item basis and also as a summary measure using methods such as mixed models analysis of variance or GEE that accommodate missing data and changing covariates.

The content and schedule of reports to be available to the core team, the SMC, and the full team will be detailed in the Study Monitoring Plan that will be developed prior to the opening of accrual to the study.

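### The culture-only treatment-failure definition omits the deaths and early discontinuations that section 9.3.2 counts as failures, and Kaplan-Meier is named for non-fatal events that death can preclude

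*Protocol*

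**What the plan says.** **Failure.** The Schema (Stage 1 and Stage 2 Evaluations) states: "Treatment failure for any participant is defined as a positive culture from a CSF sample collected at week 10". Section 3.0 gives the same culture-based rule, and neither place mentions death. Section 5.1.1, under Management of Mycological Failure at Week 10, has a related label: "participants with mycological failure (ie, whose most recent CSF culture is positive").

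Section 9.3.2 uses another rule. Its first reason for 48 per group is a 90% confidence interval for "culture negativity (early discontinuation or death = fail) within a dose or within ampho B-based regimens no wider than 25" per cent. Objective 1.3.4 refers to clinical and mycological success at week 10, but success is not defined for this trial. Section 2.1.1 gives a definition only for the earlier dose-ranging trial, where success meant being alive with a negative CSF culture.

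**Time to event.** Section 9.5.2: "Survival and other measures of time-to-event from study entry will be summarized with Kaplan-Meier estimates". Time to CSF sterility (objective 1.3.4) falls under this sentence. Section 9.3.3 says that the "proportion with IRIS at pre-specified time points such as 8 or 12 weeks will be estimated by Kaplan Meier methods", with Greenwood intervals. Neither section says how a death before the event is handled.

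**The concern.** Two rules in one protocol classify the same participant in opposite ways. Under the Schema and section 3.0, only someone with a week-10 sample can fail. A regimen with more early deaths then has fewer participants who can be counted as failures.

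The estimator raises a related problem. Someone who dies with a positive culture will never clear it, and someone who dies after starting ART will not develop IRIS later. If such deaths are treated as ordinary censoring, one minus Kaplan-Meier estimates what would happen if nobody died. That is not the proportion who become sterile or develop IRIS, and it is higher than that proportion.

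Section 9.3.2 lists both the rate of clearance and the proportion who clear among the inputs to Stage 2 dose selection, and objective 1.2.2 is to choose a dose for the next trial. The definitions should therefore not be open to either reading.

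**Working it through.** **1. The plan's own figures (section 9.3.2), by normal approximation.**
- 90% interval width at p = 0.5, n = 48: 2 × 1.645 × √(0.25/48) = 0.237, within the 25% limit.
- Power for 50% against 75%, 48 per group, one-sided 0.10: (0.25 − 1.2816 × √(2 × 0.625 × 0.375/48)) / √((0.25 + 0.1875)/48) = (0.25 − 0.1267)/0.0955 = 1.29, so power is 90%.

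Both reproduce. The interval criterion already assumes that death is a failure.

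**2. The two rules side by side.**

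| Participant | Schema and 3.0 | 9.3.2 |
|---|---|---|
| Dies on day 20, week-2 culture positive | not a failure | failure |
| Stops treatment in week 3, week-2 culture positive (6.3.22 requires no further cultures) | normally not a failure | failure |
| Negative at week 4, alive and on treatment at week 10 | not a failure | success |
| Alive, week-10 culture positive | failure | failure |
| Alive, on treatment, last culture positive, week-10 sample missed | not a failure | not stated |

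**3. Size of the difference in failure.** Inputs: n = 48 (9.3.2). Mortality of 25% is the 10-week figure for the ampho B plus flucytosine study in section 2.1.2. The 10% culture positivity among survivors is my assumption.
- Deaths: 48 × 0.25 = 12. Survivors: 36. Culture positive: 3.6.
- Culture-only: 3.6/48 = 7.5% of all, or 3.6/36 = 10% of survivors.
- With death as failure: (12 + 3.6)/48 = 32.5%. With positivity of 5% or 20% instead: 28.8% or 40.0%.
- At mortality of 15%, 25% and 43%, culture-only failure among all participants falls (8.5%, 7.5%, 5.7%) while failure including death rises (23.5%, 32.5%, 48.7%).

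**4. Time to sterility.** Assume constant hazards over 10 weeks, with the same death hazard before and after clearance. Net mortality m is then the 10-week risk of death if clearance did not occur. Let K be one minus Kaplan-Meier with deaths censored.

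λs = −ln(1 − K), λd = −ln(1 − m), and cumulative incidence = λs/(λs + λd) × [1 − (1 − K)(1 − m)].

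For K = 70% and m = 25%: λs = 1.204, λd = 0.288, so 1.204/1.492 × (1 − 0.30 × 0.75) = 0.807 × 0.775 = 62.6%.

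| Net mortality | Cumulative incidence when K = 70% | Gap (points) |
|---|---|---|
| 15% | 65.6% | 4.4 |
| 25% | 62.6% | 7.4 |
| 33% | 60.0% | 10.0 |
| 43% | 56.5% | 13.5 |

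The 15% is the upper figure for very early mortality in section 9.3.1. The 43% is the highest 10-week mortality tabulated in section 2.1.2 (7/16). With K = 50% or 90%, the gap runs from 3.4 to 14.2 points over the same mortality range. Earlier deaths widen it. In an invented pattern of 48 participants, 12 die before clearing (7 of them before week 2) and 33 clear; Kaplan-Meier then gives 89% against 33/48 = 69%.

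**5. IRIS.** Same formula, with time running from ART start. For K = 20%, post-ART mortality of 5% or 10% (my assumption) gives 19.5% or 19.0%, a gap of 0.5 to 1.0 point. At 30% it is 16.9%, a gap of about 3 points.

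**The case against.** **Deaths are not ignored overall.** Survival is a primary outcome (9.2.1.3). Time to death and the combined rates of DLT and death are objective 1.3.3. More than six very early deaths in a cohort trigger review (9.3.1), and early CM mortality is a named input to Stage 2 dose selection (9.3.2). This stands. A reader might infer that a dose with more deaths would be selected because of the failure label; the protocol does not support that.

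**The treatment-failure sentence may be a management label.** Section 3.0 follows it with the option to stop study treatment, and it is not among the section 9.2 outcomes. This also stands, so the protocol does not show that failure will be understated. That follows only if the label is carried into analysis. The wording covers any participant, however, and follows the primary efficacy measure in the Schema and section 3.0, so the reading is open.

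**Censoring of deaths is an inference.** The protocol states it only for the secondary Stage 1 analysis of DLT (9.3.1). An analysis plan not shown may handle deaths in sterility and IRIS correctly. In addition, 9.5.2 lists CSF clearance before week 10 as a dichotomous outcome, and objective 1.3.4 concerns covariate effects, for which cause-specific hazards that censor at death are legitimate. The point rests on the estimator the protocol does name for a proportion.

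**Two larger figures are tempting and should not be used.**
- Table 2-3 shows 3/151 culture positive against 42/151 failures in the fluconazole arm. The other 39 had no CSF sample and are not counted as deaths. Section 2.1.1 uses the table to argue that counting missing cultures as positive inflates failure.
- Setting 60% sterile with 25% dying first gives one minus Kaplan-Meier of 74%. The death hazard is then −ln(0.15) × 0.25/0.85 = 0.558, a net mortality of 43%, the extreme of the cited studies.

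**Conclusion.** The point holds in a limited form. The failure definition in the Schema and section 3.0 is not reconciled with section 9.3.2, and week-10 success is undefined. If the culture-only rule were used for efficacy, most of the failures counted by 9.3.2 could disappear (7.5% against 32.5% under the stated assumptions).

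Kaplan-Meier with deaths censored would overstate the proportion sterile by about 7 points at an assumed 25% net mortality, and by about 4 to 14 points over 15% to 43%. This assumes constant hazards and that deaths would in fact be censored. The IRIS effect is likely small, because time starts at ART initiation, which section 9.3.3 recommends deferring to Step 3 or 4. A claim that IRIS is materially overstated is not supported.

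A reader might also infer that the sample size is wrong. It is not affected, because 9.3.2 already treats death as failure.

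**What to change.** - **One efficacy rule for analysis.** Use the 9.3.2 rule as the week-10 definition and state it for objective 1.3.4. Success means alive with a negative CSF culture obtained by week 10 (cultures stop once negative, 6.3.22); death or early discontinuation is failure.
- **Rename the label.** In the Schema and section 3.0, call the culture-only definition mycological failure. Section 5.1.1 already uses that term for the most recent culture, so the wordings must be reconciled. Which one governs management is not a statistical question and is left to the protocol team.
- **Living but unsampled participants.** Report them as a separate category, with a sensitivity analysis counting them once as failures and once as successes. Counting them only as failures would repeat the practice that section 2.1.1 criticises.
- **Estimator.** In 9.3.3 and 9.5.2, estimate time to sterility and the proportion with IRIS by Aalen-Johansen cumulative incidence with death as a competing event. Keep Kaplan-Meier for survival and cause-specific hazards for covariate effects.

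The cost is wording in the Schema and sections 1.3.4, 3.0, 5.1.1, 9.3.3 and 9.5.2. It needs standard software and no new data, visits or participants.

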**Cohort 1 was closed after data from the first 29 participants were reviewed.**

Cohorts 2A and 2B **opened to accrual on Friday, October 7, 2011.** **Up to** 32 participants **will be** randomized 3:1 to an induction step of either fluconazole (at 1600 mg/day) or ampho B-based regimen.

.

**Data through week 2 from all participants in Cohort 2 will be reviewed before a decision about opening Cohort 3 is made. If safe to continue, Cohrt 3 will be opened.**

**Up to** 32 participants **will be enrolled in** Cohorts 3A and 3B **and** randomized 3:1 to an induction step of either fluconazole (at 2000 mg/day) or ampho B-based regimen.

.

**After data through week 10 from all participants in the last Stage 1 cohort are available, a r**eview of **all available** Stage 1 data **will occur**; MTD of fluconazole **will be** determined; relationship of fluconazole dose to efficacy **will be** examined; determination of doses to be tested in Stage 2 **will be** made.

Stage 2 **will open**; **approximately** 96 participants **will be** randomized to receive 1 of up to 3 fluconazole doses **or fluconazole plus 5FC** or to receive ampho B-based regimen in the induction step.

Protocol **will be** amended.

A5225/HiFLAC Stage 1 Flow Chart #1

Randomization

Step 3:

400 mg fluconazole

(or 600 mg w/ RIF)

Step 3:

400 fluconazole

(or 600 mg w/ RIF)

Step 2:

400-800 mg **daily**

fluconazole

Cohort 1

Step 1:

1200 mg fluconazole

4-10 wks

Step 4:

200 mg

fluconazole through wk 24

Step 1:

ampho B based regimen

(~ 2 wks)

Step 4:

200 mg

fluconazole through wk 24

ifCSF-neg.

by wk 8

at wk 10

ifCSF neg.

by wk 8

**Cohort 1 was closed after data from the first 29 participants were reviewed.**

if TLT before wk 2

at week 10

atweek 10

at wk 10

at week 2

A5225/HiFLAC Stage 1 Flow Chart #2

Cohort 2

Randomization

**(Cohort 2 was opened to accrual on Friday, October 7, 2011.)**

Step 1:

1600 mg fluconazole

4-10 wks

Step 3:

400 mg fluconazole

(or 600 mg w/ RIF)

Step 4:

200 mg

fluconazole through wk 24

Step 1:

ampho B based regimen

(~ 2 wks)

Step 3:

400 mg fluconazole

(or 600 mg w/ RIF)

Step 4:

200 mg

fluconazole through wk 24

Step 2:

800 mg **daily**

fluconazole **or maximum locally approved dose**

Week 2

if TLT before wk 2

at wk 10

if CSF neg.

by wk 8

at week 10

at wk 10

ifCSF neg.

by wk 8

at week 2

at week 10

If / when safe to continue, Cohort 3 mayopen.

A5225/HiFLAC Stage 1 Flow Chart #3

Cohort 3

Randomization

Step 1:

2000 mg fluconazole

4-10 wks

Step 3:

400 mg fluconazole

(or 600 mg w/RIF)

Step 4:

200 mg

fluconazole through wk 24

Step 1:

ampho B based reg.

(~ 2 wks)

Step 3:

400 mg fluconazole

(or 600 mg w/ RIF)

Step 4:

200 mg

fluconazole through wk 24

Step 2:

800 mg **daily**

fluconazole **or maximum locally approved dose**

if TLT before wk 2

at wk 10

ifCSF neg.

by wk 8

at week 10

at wk 10

ifCSF neg.

by wk 8

at week 2

at week 10

A5225/HiFLAC Stage 2 Flow Chart

at week 2

at week 10

Randomization

Step 1:

***1-3***

fluconazole cohorts

(4-10 wks)

Step 4:

200 mg fluconazole through wk 24

Step 3:

400 mg fluconazole (or 600 mg w/ RIF)

Step 1: ampho B based reg.

(~ 2 wks)

Step 2:

800 mg daily

fluconazole or maximum locally approved dose

Step 3:

400 mg fluconazole

(or 600 mg w/ RIF)

Step 4:

200 mg

Flucon-azole through wk 24

if TLT before wk 2

at wk 10

if CSF neg.

by wk 8

if CSF-neg by wk 8

at wk 10

at week 10

## 1.0 HYPOTHESES AND STUDY OBJECTIVES

### 1.1 Hypotheses

1.1.1 Fluconazole alone at a dose of 1200, 1600, and/or 2000 mg/day will be well tolerated and safe in participants presenting with HIV-associated CM.

1.1.2 Increasing doses of fluconazole will have increasing efficacy, as follows:

1.1.2.1 Increasing microbiological (fungicidal) efficacy as measured by the mean change between dosing groups in log10 concentration of cryptococci in CSF between baseline and week 2.

1.1.2.2 Increasing clinical efficacy as measured by survival at 10 weeks.

### 1.2 Primary Objectives

1.2.1 To assess the MTD of fluconazole by comparing the safety and tolerability of induction regimens of 1200, 1600, and 2000 mg/day.

1.2.2 To determine whether the safety and efficacy of high induction-dose fluconazole therapy support development of a phase II/III trial, and, if so, to select the most appropriate fluconazole dose regimen (based on safety and efficacy data from this study) to be evaluated in that trial.

### 1.3 Secondary Objectives

- - 1. To compare the clinical and fungicidal effects of different induction regimens of fluconazole during induction at weeks 2, 4, 6, 8, and 10.
    2. To assess functional status (prior to onset of current CM illness, at study entry, at week 10, and at premature treatment or study discontinuation) and to assess neurological status [at entry, weeks 2, 10, 24, and at progression of symptoms and premature treatment or study discontinuation].

1.3.3 To assess the time to death in each cohort and the combined rates of DLT and death.

1.3.4 To describe the effect of baseline clinical, neurological, and mycological characteristics on clinical and mycological success at week 10 and on time to CSF sterility.

- - 1. To assess the length of hospitalization between study entry and hospital discharge and for any subsequent readmission for the treatment of CM.
    2. To assess the incidence of progression of symptoms and its components among all participants receiving ART during the study.

1.3.7 To estimate the tolerability, toxicity, and efficacy of an ampho B-based regimen in the setting of non-U.S. sites for the purposes of planning additional studies.

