Dose adjustment guidelines for ampho B side effects are described in section 5 of the A5225/HiFLAC MOPS. Step 2 has been included in the protocol for participants who discontinue ampho B because of ampho B intolerance. Each site will be allowed to determine the appropriate Step 2 dose of fluconazole, either 800 mg daily or the maximum locally approved dose.

ART Initiation and Potential Drug-Drug Interactions

Evidence-based guidelines are not available for optimal timing of ART initiation in the setting of acute CM. Site clinicians may initiate ART when they feel it is appropriate to do so. However, because fluconazole substantially increases NVP levels and may increase hepatotoxicity [Geel 2004], NVP-based ART may be used only when participants are taking fluconazole at a dose of ≤ 400 mg. Because NVP-based ART is commonly employed in resource-limited settings, site clinicians are advised to seek alternative antiretroviral drugs (ARVs) for participants on higher doses of fluconazole.

There is the potential for two-way interactions between fluconazole and non-nucleoside reverse transcriptase inhibitors (NNRTIs) and drugs belonging to the class of protease inhibitors (PIs). As mentioned previously, fluconazole is an inhibitor of CYP450 3A4 and, to a lesser extent, 2C8, 2C9, and 2C19 [Niwa 2005]. Therefore, levels of medications that are substrates of CYP450 enzymes may be raised in the presence of fluconazole. These include the NNRTIs NVP and EFV, and the PIs nelfinavir, amprenavir, fosamprenavir, lopinavir, and atazanavir.

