6.3.6 ART (Initiation and Modification)

All modifications to ART must be recorded on the CRF. Modifications include initiation as well as any changes in dose or formulation, interruptions of 2 or more consecutive days, or discontinuations for any reason.

Although initiation of ART prior to week 4 is discouraged for participants taking high dose fluconazole, participants who initiate ART that does not contain NVP prior to Step 3 may remain on study. Participants who initiate NVP while taking high dose fluconazole (ie, at a dose higher than 400 mg daily) must be discontinued from study treatment.

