6.3.9 Clinical Assessments

At the visits indicated in the SoE, clinical assessments should be conducted and should be driven by any previously identified or new signs or symptoms or diagnoses that the subject has experienced since the previous visit.

Vital Signs

Vital signs (temperature, pulse, respiratory rate, and blood pressure) must be recorded on the CRFs.

Signs and Symptoms

At entry, all signs and symptoms occurring within 3 days prior to entry must be recorded and keyed within 48 hours. In Stage 1, Steps 1 and 2, beginning on Day 1, all Grade ≥ 3 signs, symptoms, and toxicities, and those that lead to a change in treatment, regardless of grade, must be recorded and keyed within 48 hours. For Stage 1, Steps 3 and 4, and in all of Stage 2, regardless of step, all Grade ≥ 3 signs, symptoms, and toxicities, and those that lead to a change in treatment, regardless of grade, must be recorded.

In addition, in Stages 1 and 2, the identification of symptoms that lead to the evaluations described under section 6.2.3 must be brought to the attention of the study core team via e-mail within 2 weeks after the site’s becoming aware of these symptoms.

Sites must refer to the DAIDS Table for Grading the Severity of Adult and Pediatric Adverse Events, Version 1.0, dated December 2004, which can be found on the DAIDS RSC Web site: [http://rsc.tech-res.com/safetyandpharmacovigilance/.](http://rsc.tech-res.com/safetyandpharmacovigilance/.  ) .

Diagnoses

All diagnoses identified by the ACTG criteria for clinical events and other diseases must be recorded and keyed within 48 hours.

Classification of Progression of Symptoms

In addition, using data generated from evaluations conducted as described under 6.2.3, investigators will classify progression of symptoms as one of the following:

1) microbiological failure (i.e., positive CSF culture)

2) complication of CM (e.g., obstructive hydrocephalus or vascular complications such as venous or arterial thrombosis)

3) IRIS to CM causing increased inflammation after exposure to ART

4) a new CNS OI (e.g., toxoplasmosis, PML, CNS lymphoma)

5) possibly related to CM but mechanism indeterminate

6) other defined complication unrelated to CM.

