9.2.3 Exploratory Outcomes (to be described in separate analysis plans)

9.2.3.1 Pharmacology (see section 10.0).

9.2.3.2. Antifungal drug susceptibility of cryptococcal isolates.

9.2.3.3 Ability of LFCrAg assay to detect cryptococcal antigen in stored urine, serum, plasma, and CSF.

### 9.3 Sample Size and Criteria for Stages 1 and 2

9.3.1 Stage 1

The team feels that standard dose (400 mg/day) fluconazole would have about 5% DLT as defined in this study. To avoid the toxicity and difficulty of administration of ampho B, the team feels that ≤25% DLT would be acceptable. In the international setting and in participants with HIV and AIDS, the team also has concluded that there likely will be up to a 15% very early mortality rate in any cohort due to CM and/or HIV, not to the dose of fluconazole. Including participants who received very little fluconazole in safety evaluations to determine dose escalation could bias the evaluation either to be too high (if early deaths without toxicity are considered to be DLTs) or too low (if early deaths without toxicity are included in the denominator of the DLT rate). Thus, for primary safety evaluations, very early deaths (prior to Day 4) will not be included in the decision rule whether they experienced a DLT prior to early death or not [French, 2002; Okongo, 1998; Hakim, 2000; van der Horst, 1997; Brouwer, 2004; Pappas, 2004; Bicanic, Meintjes, et al, 2008; and Milefchik, 2008]. Should more than 6 very early deaths be seen in a cohort, enrollment to the cohort will by paused while the team evaluates the events carefully in conjunction with the SMC to consider if there should be study modifications. Secondary evaluations prior to escalation will include all subjects in a failure-time analysis of DLT with early deaths censored if DLT did not occur prior to death.

The dose escalation rule to be used in Stage 1 is:

- 0-3 DLTs; escalate to the next higher dose.
- 4-9 DLTs; do not escalate. This is the MTD.
- > 9 DLTs; the prior dose is the MTD.

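### Objective 1.3.6 measures progression of symptoms among participants who receive ART, so worsening in those who die or leave before ART is not counted

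*Protocol*

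**What the plan says.** **Population.** Protocol section 1.3 (objective 1.3.6) reads "To assess the incidence of progression of symptoms and its components among all participants receiving ART during the study". It gives no time origin and does not say how death before ART is handled.

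**When ART starts.** Section 2.2 leaves timing to the clinician: "Site clinicians may initiate ART when they feel it is appropriate to do so". Section 6.3.6 says that "initiation of ART prior to week 4 is discouraged for participants taking high dose fluconazole". The Secondary Endpoints subsection (9.3.3) adds that "it is recommended that ART not be initiated until Step 3 or 4". The eligibility criteria in section 4 do not exclude people already on ART.

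**Who is evaluated for progression.** Section 6.2.3 applies to any participant whose CNS signs or symptoms recur or worsen significantly, whether or not on ART. Under section 6.3.9, "investigators will classify progression of symptoms as one of the following", and six classes follow: microbiological failure, complication of CM, IRIS to CM, a new CNS opportunistic infection, indeterminate but possibly CM-related, and a defined complication unrelated to CM. Only IRIS is defined by exposure to ART.

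**The one ART-timed analysis described.** Section 9.3.3 plans "The time from ART start to development of IRIS" by Kaplan-Meier methods. It covers IRIS and no other class.

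**Early mortality.** Section 9.3.1 assumes that "there likely will be up to a 15% very early mortality rate in any cohort due to CM and/or HIV", where very early means before Day 4.

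**The concern.** An incidence needs a group fixed at the time from which events are counted. Receiving ART at some point in 24 weeks is usually known only later, and it requires being alive and on study when ART starts. Two participants with the same worsening in week 2 are treated differently: the one who recovers and starts ART at week 6 belongs to the group, and the one who dies in week 3 without ART does not.

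For IRIS the restriction is right, because nobody is at risk before ART. For the other five classes, and for progression overall, it selects on survival. Early worsening in this disease is of direct interest when judging an induction regimen, and that is the part which can drop out. The reported figure could be read as the progression rate of the trial population when it is the rate among those who reached ART.

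The selection may also differ between arms. Under section 6.2.2, ampho B participants who do not enter Step 2 are expected in Step 3 after about 2 weeks whatever the culture shows. Fluconazole participants receive at least 4 weeks of induction and then leave Step 1 on a negative culture or at week 10. If ART follows Step 3 or 4, the time to be survived before joining the group differs by arm.

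**Working it through.** **1. A protocol figure that can be checked.** The protocol states no incidence of progression, so there is none to reproduce. Its early-death assumption can be tested against section 9.3.1, which gives the chance of a review (more than 6 very early deaths) as 6%, 61% and 90% at true rates of 15%, 30% and 40%. With 24 participants, the binomial probability of 7 or more deaths is 5.7%, 61.1% and 90.4%. These agree.

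**2. Effect of the restriction.** Define:
- d = share of participants who never receive ART on study;
- s = share of ART recipients who progress;
- q = share of those never receiving ART who progress.

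Objective 1.3.6 reports s. The all-participant incidence is (1 − d)s + dq. The difference, all-participant minus ART-only, is d(q − s). It is positive if q > s, zero if q = s and negative if q < s.

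**3. Illustration.** The documents give none of d, s or q. I assume s = 20% and 48 participants per group (the two-stage target in section 9.3.2). The value d = 15% matches the protocol's upper figure for deaths before Day 4; 25% and 35% are further assumptions.

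| d | Not in the group, of 48 | q = 0% | q = 20% | q = 50% | q = 80% |
|---|---|---|---|---|---|
| 15% | 7.2 | 17.0% | 20.0% | 24.5% | 29.0% |
| 25% | 12.0 | 15.0% | 20.0% | 27.5% | 35.0% |
| 35% | 16.8 | 13.0% | 20.0% | 30.5% | 41.0% |

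Example: 0.85 × 0.20 + 0.15 × 0.50 = 0.170 + 0.075 = 24.5%. The ART-only figure is 20% in every cell.

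**4. If arms were compared.** Take d = 15% in one arm and 30% in the other, with s = 20% in both. The ART-only rates are equal. With q = 50%, the all-participant rates are 24.5% and 0.70 × 0.20 + 0.30 × 0.50 = 29.0%. With q = 0%, they are 17.0% and 14.0%, so the order reverses.

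**5. Time origin.** If recipients are counted from entry, someone starting ART at week 4 is certain to be alive for 4 of 24 weeks (17%), and someone starting at week 10 for 10 of 24 (42%). If they are counted from ART start, all pre-ART worsening is left out. Under either reading, people lost before ART are missing.

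**The case against.** **ART recipients are a legitimate population.** Worsening after ART has to be sorted into IRIS, culture-positive failure, new infection and other causes, and reporting all classes in recipients helps to interpret the IRIS figure. This stands for post-ART worsening with the clock at ART start. It does not make the group suitable for progression overall.

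**Nothing forbids a wider analysis, and related outcomes are unrestricted.** CSF cultures and survival are primary outcomes (9.2.1), CM recurrence or relapse is outcome 9.2.2.3, and neurological findings at progression are in 9.2.2.1. A reader might infer that progression before ART goes unrecorded; section 6.2.3 shows that it is evaluated in everyone. The gap is in the stated analysis population, and these outcomes cover the six-class result only in part.

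**Details may be in the analysis plan.** Section 9.3.3 promises a detailed plan before secondary analyses, so an unstated time origin or competing-event rule is not itself an error. The population, however, is fixed in the protocol.

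**The rate need not be too low.** A reader might infer that leaving out the sickest biases it downward. That requires q > s, which no document shows. Deaths before Day 4 leave little time for a progression evaluation, so a low q is plausible, and the ART-only rate would then be too high.

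**The loss need not be one in six or more.** A reader might pool week-2 deaths in the ampho B-containing studies summarised in section 2.1.2: (2 + 5 + 7 + 3 + 4 + 6)/(16 + 16 + 30 + 22 + 23 + 47) = 27/154 = 17.5%. That counts deaths in other studies, none of them fluconazole alone and one using a 5-day course. It does not count losses before ART here, where people may already be on ART or start early.

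**No comparison of arms is stated in 1.3.6.** Correct. Section 9.3.3 foresees some secondary analyses of all fluconazole against all ampho B, without naming this one.

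**Conclusion.** The point holds in a limited form. For participants not on ART at entry, objective 1.3.6 conditions the incidence of progression and its components on a later, non-randomised event. Worsening in people who die or leave before ART is not counted. For the five non-IRIS classes and for progression overall, the result is a rate among those who reach ART.

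Its difference from the all-participant rate is d(q − s), and the protocol supplies none of the three terms. At d = 15% and s = 20%, the difference runs from −3 to +9 percentage points for q from 0% to 80%. That range rests on assumed inputs and is not an estimate of bias. A claim that the rate is biased low, or that one arm would be favoured, goes beyond the documents; a distortion between arms arises only if arms are compared and d or q differs between them.

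The IRIS analysis timed from ART start is sound. The objective is secondary and unpowered, and MTD, EFA and survival are not affected. The change is still worth making because it is nearly free.

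**What to change.** Reword objective 1.3.6 and give it two parts.

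1. **All randomised participants, from study entry.** Report the cumulative incidence of progression overall and of each class in section 6.3.9, with death as a competing event.
2. **ART recipients.** Keep this analysis for IRIS and post-ART worsening. Each participant enters at ART start, or at study entry if already on ART, and only later events count. This extends the time origin that section 9.3.3 already uses for IRIS to the other classes.

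If arms are compared on progression, part 1 should carry the comparison.

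The cost is a change of wording and one additional descriptive analysis. Sections 6.2.3 and 6.3.9 already provide evaluation and classification in all participants who worsen, and ART dates and deaths are recorded, so no new data or participants are needed.
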